## Introduction

Cerebral infarction, a life-threatening neurodegenerative disease, predominantly affects older adults and is classified as an ischemic cerebrovascular event [1]. Due to the various degrees and types of brain damage it causes—such as brain tissue lesions, structural damage, neuronal death, and dysfunction—it remains one of the leading causes of disability and death [2,3]. According to the 2019 Global Burden of Disease study, the age-standardized incidence rate of cerebral infarction in China was 144 per 100,000, and the age-standardized prevalence was 1255.9 per 100,000. With the acceleration of population aging, the burden of this disease is expected to continue rising [4].

The acute phase of cerebral infarction progresses rapidly, with most patients entering the recovery phase approximately 2 weeks after onset, which typically lasts about 6 months. The recovery phase is crucial for regaining cognitive ability, memory, and motor functions, thereby enhancing daily living capabilities. Hence, rehabilitation during this stage is a hot topic in clinical research [5]. Core treatment strategies during this phase primarily include antiplatelet therapies, such as aspirin, clopidogrel, sarpogrelate, and cilostazol, aimed at reducing stroke recurrence and improving neurological function [6-8]. However, these treatments have yet to effectively address the high recurrence and disability rates.

Multiple clinical studies have confirmed that traditional Chinese medicine (TCM) therapies—such as Buyang Huanwu decoction and acupuncture—can significantly improve clinical symptoms during the recovery phase of cerebral infarction. These include reducing the recurrence rate of cerebral infarction, enhancing neurological function, and mitigating the severity of neurological deficits, making TCM a vital component of stroke rehabilitation [9-14].

We have used Qizhi Jieyu pill, composed of traditional herbs such as *Panax notoginseng* and leech, in clinical practice for over 10 years to treat patients during the recovery phase of cerebral infarction. Preliminary, retrospective analysis of 152 cases indicates that Qizhi Jieyu pill may alleviate clinical symptoms, improve quality of life, and reduce recurrence. This suggests its potential as an important therapeutic option during the recovery phase. However, there is still a lack of high-quality clinical studies to validate its efficacy and safety.

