#### Exclusion Criteria

Criteria for exclusion from the study include the following:

Patients diagnosed with intracranial hemorrhagic disease by head CT or MRI.Patients with abnormal clinical laboratory tests, including alanine aminotransferase or aspartate aminotransferase ≥2.5 times the upper limit of normal or creatinine above the upper limit of normal.Patients unable to understand or comply with the study protocol due to severe psychiatric, cognitive, or emotional disorders.Patients with other diseases affecting limb mobility that may impact neurological assessments.Women who are pregnant, breastfeeding, or planning to conceive in the near future.Patients with a suspected or confirmed history of alcohol or drug abuse within 6 months prior to onset.Patients with a known or suspected allergy to the investigational drug or those with an allergic constitution.Patients who have participated in another clinical trial within the last 3 months.Other situations judged by the investigator to reduce the likelihood of enrolment or complicate enrolment.

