### Intervention

Referring to the guidelines for clinical management of cerebrovascular diseases in China (second edition) [20], both groups will receive conventional rehabilitation training guidance, including assessment and rehabilitation of cognitive function, speech ability, swallowing function, limb motor and sensory function, balance, psychological state, and daily living abilities. They will also receive standard treatments such as antiplatelet therapy, lipid-lowering and blood pressure control, plaque stabilization, and electrolyte balance maintenance.

On the basis of conventional treatment, the study group will take Qizhi Jieyu pills, 9 g per dose, twice daily after meals. The control group will receive conventional treatment only. The intervention period is 12 weeks, with a total follow-up period of 48 weeks.

All TCM drugs with the same therapeutic effect as the investigational drug (including those with similar indications or efficacy stated in the instructions) are prohibited during the study. All concomitant medications and treatments (ie, for other diseases) must be recorded in the concomitant medication log.

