#### Safety Outcomes

Safety will be assessed using the following monitoring indicators:

Vital signs, including temperature, blood pressure, respiration rate, and heart rate, checked every 12 weeks.Routine tests, including blood, urine, and stool tests, every 12 weeks.Other labs and diagnostics, including electrocardiograms, liver function tests (alanine aminotransferase, aspartate aminotransferase, gamma-glutamyltransferase, alkaline phosphatase, and total bilirubin), and kidney function tests (blood urea nitrogen and creatine), every 12 weeks.Adverse events: From the time the participant enters the study until the final follow-up, adverse events will be monitored for 48 weeks. All information related to adverse events will be carefully recorded at all times. Serious adverse events refer to any unexpected clinical events occurring at any dose that result in hospitalization, prolongation of existing hospitalization, disability, impaired ability to work, life-threatening conditions or death, or congenital malformations. Serious adverse events will be reported to the study center and the principal medical ethics committee. In addition, they will be reported to the National Medical Products Administration within 24 hours. Meanwhile, we will specifically record adverse events potentially related to animal-derived components, such as itching, rash, allergic reactions, and gastrointestinal discomfort.

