#### Statistical Analysis Plan

A statistical analysis plan was formulated prior to the start of the study. It will be finalized after discussion among the statisticians, principal investigators, and sponsor before database lock. This plan describes only the standard statistical requirements.

Statistical analysis will be conducted using SAS version 9.4. All hypothesis tests will be 2-sided, with a significance level of α=.05. *P* values less than or equal to .05 will be considered statistically significant.

For continuous variables, mean, SD, minimum, maximum, and median values will be used for descriptive statistics. Independent samples *t* tests (for normally distributed data) or Wilcoxon rank-sum tests (for non-normally distributed data) will be used for hypothesis testing. Normality of continuous variables will be assessed using the Shapiro-Wilk test before choosing appropriate parametric or nonparametric tests.

For categorical variables, frequency and percentages will be used for description. Chi-square tests or Fisher exact tests will be used for hypothesis testing. Ordinal variables will be analyzed using the Wilcoxon rank-sum test.

Logistic regression will be used to control for confounding factors affecting the outcome measures. We will also analyze the association between syndrome evolution patterns and therapeutic efficacy. In parallel, multivariate linear regression will be used to explore the relationship between outcomes and potential confounders, such as baseline NIHSS score, study center, age, and sex. For adverse events potentially associated with animal-derived components—including itching, rash, allergic reactions, and gastrointestinal discomfort—we will conduct attribution analysis and report their incidence separately.

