Qizhi Jieyu pill consists of 26 herbal and animal-derived medicinal components, including *Panax notoginseng, Hirudo, Buthus martensii, Scolopendra, Pheretima, Gastrodia elata, Uncaria, Cassia seed, Bombyx batryticatus, Acorus tatarinowii, Polygala, Typhonium giganteum,* and *Astragalus*, among others. It is formulated to remove blood stasis and phlegm, unblock collaterals to extinguish wind, and tonify the spleen and kidneys. Astragaloside IV, a major active compound of *Astragalus*, may promote angiogenesis via the silencing regulatory protein 7 (SIRT7)/vascular endothelial growth factor A (VEGFA) signaling pathway to improve brain tissue damage postcerebral infarction [24]. Astragaloside I has been shown to activate the transforming growth factor-β (TGF-β)/Smad signaling pathway and exert antioxidant effects, significantly improving cognitive dysfunction in rats with cerebral infarction [25,26]. *Gastrodia elata* can effectively reduce brain necrosis area, infarct volume, and inflammatory factor levels in rats with cerebral ischemia-reperfusion injury, with mechanisms involving the modulation of gut microbiota [27]. In addition, gastrodin, an active ingredient in *Gastrodia elata*, can increase the expression of miR-20a-5p in circulating exosomes and X-linked inhibitor of apoptosis protein (XIAP) in the ischemic hemisphere, thus promoting neurological recovery in rats with middle cerebral artery occlusion [28]. Ginsenoside Rg1 (G-Rg1), a key component of *Panax ginseng*, can reduce neural injury, infarct volume, and blood-brain barrier permeability in focal cerebral ischemia in rats, potentially through downregulation of protease-activated receptor-1 (PAR-1) expression [29]. These studies provide mechanistic support for the potential of Qizhi Jieyu pill as an effective treatment for cerebral infarction.

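### The adverse events singled out for dedicated recording, attribution and separate reporting leave out bleeding, although a leech-containing pill formulated to remove blood stasis is added to antiplatelet therapy

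*Protocol article*

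**What the plan says.** Three parts of the protocol article bear on this point.

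- **The targeted list.** Beyond general adverse event recording, Safety Outcomes singles out "adverse events potentially related to animal-derived components, such as itching, rash, allergic reactions, and gastrointestinal discomfort". The Statistical Analysis Plan section repeats the list, "including itching, rash, allergic reactions, and gastrointestinal discomfort", and states that for these events "we will conduct attribution analysis and report their incidence separately". No other class of event gets this treatment.
- **The product and its background treatment.** The Introduction says the pill is composed of herbs such as Panax notoginseng "and leech, in clinical practice for over 10 years"; Principal Findings lists Hirudo among its components. Of the product as a whole, Principal Findings says: "It is formulated to remove blood stasis and phlegm, unblock collaterals to extinguish wind". Under Intervention, both groups have conventional care: "They will also receive standard treatments such as antiplatelet therapy". The study group takes the pill on top of that.
- **General safety capture.** Under Safety Outcomes, all adverse events are recorded over 48 weeks, and serious ones are reported onward. Table 1 has adverse events, and brain CT or MRI, at all four post-baseline visits. The safety set, in the section on analysis datasets, is restricted to randomized participants who took at least one dose of the pill and had a post-baseline safety evaluation.

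**The concern.** The article does not leave its events of particular interest to another document. It chooses them, names them twice and attaches an analysis to them. The stated criterion is a possible link to animal-derived components, and leech is one of those. From the article's own description of the product and the background treatment, bleeding is an obvious candidate for such a list, and gastrointestinal discomfort does not cover gastrointestinal bleeding.

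Safety is part of the trial's stated aim. If itching is asked about, attributed and tabulated while bleeding is not, the two kinds of event may not be captured with the same completeness. Participants and clinicians know the assignment, so prompting and reporting of bleeding may also differ between arms. A reader of the final report could then take a low bleeding count as reassurance that the data collection cannot support.

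**Working it through.** The article states no figure on this point, so the check is mainly a comparison of texts.

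**Step 1: is bleeding in either list?** Safety Outcomes and the Statistical Analysis Plan section name the same four items: itching, rash, allergic reactions, gastrointestinal discomfort. Neither contains a bleeding term. Elsewhere in the Methods, haemorrhage appears in the diagnostic criteria and as an entry exclusion, not as a safety outcome.

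**Step 2: would a bleed be lost?** No. General adverse event recording covers it. A bleed that leads to hospitalization, disability, threat to life or death also meets the definition of a serious event. What is missing is the targeted question, the attribution and the separate incidence.

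**Step 3: do the other safety measures supply these?** Not as written.

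- Brain imaging is repeated every 12 weeks, but the safety indicators do not mention it, and nothing says how a haemorrhagic finding is to be recorded.
- Routine blood, urine and stool tests are every 12 weeks under Safety Outcomes. Table 1, as it reads in the text version, marks them at baseline, week 36 and week 48 only. The two places need reconciling.

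**Step 4: could bleeding be compared between arms?** Not in the safety set as defined. It requires at least one dose of the pill, which the control group does not receive.

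**Step 5: context from the group size.** The input is n = 63 per group (Sample Size Calculation). All bleeding rates here are assumptions.

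- Upper one-sided 95% bound with no bleeds among 63: 1 − 0.05^(1/63) = 4.6%.
- Chance of at least one bleed among 63, 1 − (1 − p)^63:

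| Assumed true rate p | Chance of at least one |
|---|---|
| 1% | 47% |
| 2% | 72% |
| 3% | 85% |
| 5% | 96% |

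- Power of a two-sided 5% comparison with 63 per arm is Φ{(d − 1.96·s0)/s1}. Here d is the difference in rates, s0 the standard error under the pooled rate and s1 the unpooled one.
  - 5% versus 10%: s0 = √(2 × 0.075 × 0.925/63) = 0.0469 and s1 = √((0.0475 + 0.09)/63) = 0.0467, so power is about 18%.
  - 5% versus 15%: s0 = 0.0535 and s1 = 0.0527, so power is about 46%.

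These figures follow from the sample size and assume every bleed is captured. They hold with or without a targeted question, so they do not measure the defect. They show only that bleeding evidence will be sparse and that each missed event counts. As an illustration, if only half of bleeds occurring at 2% were recorded, the recorded rate would be 1% and the chance of seeing any would fall from 72% to 47%. Nothing in the article supports that or any other capture fraction.

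**The case against.** The best defence is that this is an omission in a condensed article. Case report form prompts and safety tables usually belong to the full protocol, the list in Safety Outcomes is given as examples, and its declared scope is animal-derived components, not every important harm. Part of this stands: the list is open, and it supplements general recording. But the article did choose specific events and tie an analysis to them, leech falls within its own scope, and the analysis section names the same four.

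Four stronger readings are tempting and are not supported.

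- **That bleeding is left to spontaneous reporting or goes unrecorded.** Adverse events are a scheduled item at every post-baseline visit, diary cards are collected at each, and all events are to be recorded.
- **That the entry exclusion shows the plan already treats haemorrhage as a hazard of treatment.** The criterion, "Patients diagnosed with intracranial hemorrhagic disease by head CT or MRI", fits the diagnostic criteria, which use imaging to separate ischaemic from haemorrhagic disease. It defines the population and states no treatment-related concern.
- **That the repeated scans serve only to count recurrent infarction.** The article says recurrence is assessed on them but does not exclude other uses, and Table 1 lists them under diagnosis and monitoring, apart from effectiveness.
- **That the pill is established to raise bleeding risk.** The article never calls leech or the pill anticoagulant, and removing blood stasis is a traditional-medicine description. The concern is an inference from that description together with antiplatelet therapy.

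**Conclusion.** The point holds in a limited form. The plan gives dedicated recording, attribution and separate incidence to four kinds of event and not to bleeding, although its own account of the product and of background therapy makes bleeding a natural member of that list. Bleeds would be recorded, but perhaps less completely or less evenly between arms than the listed events, and the safety set as defined would not allow a comparison with control.

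The size is unknown. The article gives no bleeding rate and no basis for estimating how many events a targeted question would add. The conclusion rests on two assumptions: that the stated action of the pill on top of antiplatelet therapy makes bleeding plausible enough to ask about, and that prompted questions capture events more evenly than general recording in an open-label trial. This does not undermine the efficacy analysis. It is a correction worth making to the safety plan.

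**What to change.** 1. Add bleeding events (intracranial, gastrointestinal, skin or mucosal, other) to the targeted list in Safety Outcomes and to the separately reported list in the Statistical Analysis Plan section.
2. Ask about them in the same words at the existing visits in both arms.
3. State that any haemorrhagic finding on the CT or MRI already scheduled is recorded as a safety finding.
4. Report incidence by arm, and define the safety analysis so that control participants are included. Without this, reporting by arm cannot be done in the safety set as written.
5. Reconcile Safety Outcomes and Table 1 on when routine blood, urine and stool tests are done.

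For the bleeding items, the cost is a few case report form items, a few table rows and a revised safety set definition, with no new test or visit. Because recruitment began in April 2025, the change should be dated and entered in the trial registry, where the article says amendments will be recorded. Participants already seen will have visits without the targeted question, and the report should say so. How bleeding is managed clinically is outside this point.

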### Randomization

Random numbers will be generated using SAS statistical software (version 9.4), and participants will be assigned to the intervention and control groups in a 1:1 ratio. After screening and informed consent, patients will be randomly assigned to one of the two groups based on their order of enrolment. The drug number for each participant will remain unchanged throughout the study. In the case of a clinical emergency, the participant’s random code and group assignment may be unblinded.

Due to the nature of the intervention, participant and clinician blinding is not feasible. However, outcome assessors will be blinded to group assignments to minimize detection bias, especially for subjective measures such as TCM symptom scores.

### Data Collection and Management

#### Clinical Materials and Samples

All materials, clinical test results, and biological samples (blood, urine, and stool) will be stored securely at each subcenter after every follow-up and handed over to the principal investigator at the end of the study for archiving.

#### Data Recording and Storage Method

Paper-based case report forms (CRFs) will be used for this study. Although paper-based CRFs will be used, we will adopt a double-entry system and periodic data verification procedures. Digital scans of CRFs will be backed up, and a central data management team will oversee consistency and integrity across sites.

#### Data Quality Assurance Measures

Standard operating procedures will be established. All study personnel, including clinical investigators and CT and MRI technicians, will receive unified training.

All principal investigators at participating centers will be assessed and authorized by the project leader.

Requirements for filling in the CRFs will be strictly enforced. Records must be accurate, complete, and truthful. Corrections, if necessary, should be made with a single line through the error. The correction should be entered next to it, signed and dated.

Monitoring and audit standard operating procedures will be developed. Regular on-site monitoring visits will be conducted by the project leader to ensure compliance with the study protocol and verify that CRF data match the original source documents.

### Statistical Analysis

#### Definition and Selection of Statistical Analysis Datasets

Participants will be categorized into the following analysis sets:

Full analysis set: This includes all randomized participants who have at least 1 postbaseline efficacy evaluation. This is the main dataset for efficacy analysis. Missing values for primary efficacy outcomes will be imputed using the last observation carried forward method. Missing values for secondary efficacy and safety outcomes will not be imputed. For secondary efficacy endpoints and safety data, descriptive analysis and complete-case analysis will be conducted based on actual observed values. Although last observation carried forward is commonly used in clinical trials, we acknowledge its limitations in progressive conditions such as stroke recovery. We will perform sensitivity analyses using multiple imputation methods to evaluate the robustness of our results.Per protocol set: This includes all participants in the full analysis set who meet inclusion criteria, do not meet exclusion criteria, complete the treatment, and do not have major protocol deviations. This is the secondary dataset for efficacy evaluation.Safety set: This includes all randomized participants who received at least 1 dose of Qizhi Jieyu pill and had at least 1 postbaseline safety evaluation.

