#### Criteria for Case Elimination

The following are criteria for case elimination:

After enrollment, cases were found not to meet the inclusion criteria or to meet the exclusion criteria.Cases involving the use of prohibited medications as per protocol, necessitating elimination due to protocol violations.Cases in which the medication was never received or the exposure did not meet the experimental requirements.Cases with no evaluable records after medication administration.

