#### Conditions and Procedures for Participant Withdrawal

There are two routes for participant withdrawal.

Withdrawal determined by the investigator: This may occur when a participant already enrolled in the study becomes unsuitable for continued participation due to the development of complications, comorbidities, or special physiological changes. Other conditions include poor compliance, defined as taking less than 80% or more than 120% of the prescribed medication, and the use of prohibited medications as per protocol.

Participant-initiated withdrawal: According to the informed consent form, participants have the right to withdraw at any time. If a participant stops taking the medication or attending visits without formally withdrawing, they are still considered “withdrawn” (or “lost to follow-up”). Reasons for withdrawal should be documented where possible and may include feeling the treatment is ineffective, the development of intolerable adverse reactions, personal circumstances, financial reasons, or unexplained loss to follow-up.

Regardless of the reason, case report forms for withdrawn participants should be retained. The last recorded test results will be used as final data, and both efficacy and adverse events will be analyzed in the full dataset.

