### Study Procedures

Table 1 outlines the specific measurements and timepoints for data collection in this study. Eligible participants will undergo a 1-week preintervention screening period, a 12-week treatment period, and a total 48-week follow-up period. After the study begins, all enrolled participants will have follow-up visits every 12 weeks. All participants will be informed of the study through oral and written information and will be required to sign an informed consent form.

**Table 1 table1:** Clinical trial research timeline.

Item		Screening period and baseline	Visit 1	Visit 2	Visit 3	Visit 4
Visit time		–7 to 0 days	12 weeks ± 7 days	24 weeks ± 7 days	36 weeks ± 7 days	48 weeks ± 7 days

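### The primary analysis does not compare all participants as randomised: the full analysis set requires a score first due at week 12, the withdrawal and elimination rules do not fit with it, and LOCF is the primary method for later gaps

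*Protocol article*

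**What the plan says.** Five statements in the Protocol article bear on who enters the primary comparison and with which score.

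- **Analysis set.** *Definition and Selection of Statistical Analysis Datasets* defines the full analysis set (FAS): "This includes all randomized participants who have at least 1 postbaseline efficacy evaluation". It adds: "This is the main dataset for efficacy analysis".
- **Visits.** *Study Procedures* states: "After the study begins, all enrolled participants will have follow-up visits every 12 weeks". Table 1 schedules the first postbaseline NIHSS at Visit 1, week 12. *Intervention* gives 12 weeks as the length of treatment. Table 1 also lists drug distribution at later visits; that is a separate inconsistency and does not change when NIHSS is first measured.
- **Withdrawal.** *Conditions and Procedures for Participant Withdrawal* lets the investigator withdraw participants who take less than 80% or more than 120% of prescribed medication. It continues: "If a participant stops taking the medication or attending visits without formally withdrawing, they are still considered" withdrawn or lost to follow-up. Whatever the reason, the last recorded results become the final data, and efficacy is analysed in the full dataset.
- **Elimination.** *Criteria for Case Elimination* includes: "Cases in which the medication was never received or the exposure did not meet the experimental requirements". The other grounds are ineligibility found late, prohibited medication, and no evaluable records after medication. No analysis set is named.
- **Missing scores.** The datasets section says: "Missing values for primary efficacy outcomes will be imputed using the last observation carried forward method". It concedes that this method has limits in stroke recovery and adds: "We will perform sensitivity analyses using multiple imputation methods to evaluate the robustness of our results".

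**The concern.** Randomisation protects a comparison only if everyone randomised is in it, or if those left out are missing for reasons unrelated to arm and outcome. Here inclusion depends on still being present about 12 weeks after randomisation, in an open-label trial where one arm takes a pill and the other takes nothing in its place. People may leave because the pill disagrees with them or because they see no benefit, so loss during treatment may differ by arm and by prognosis.

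The rules also treat stopping the pill as leaving the study. Nothing in the article provides for follow-up to week 48 after treatment stops. Scores that are not collected cannot be recovered later, and LOCF would replace them with an earlier point on a recovery curve. What is at stake is whether the week-48 NIHSS difference reflects the treatment or the pattern of adherence and dropout.

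**Working it through.** **1. The plan's own figure, to fix the scale.** Inputs from *Sample Size Calculation*: changes of 6 (study) and 4.9 (control), SD 2.0, two-sided α = 0.05, β = 0.2.

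n per group = 2 × (1.960 + 0.842)² × 2.0² / δ²

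- δ = 6 − 4.9 = 1.1 gives n = 52, the stated figure.
- δ = 2, the difference printed in the text, gives n = 16.

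The design difference is therefore 1.1, and it is the yardstick below. The dropout allowance is 52 × 1.2 = 62.4, rounded up to 63 per arm.

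**2. How many could fall outside the FAS.** The planned 20% of 63 is 12.6 per arm. The article does not say when dropout occurs. If it is even over the four 12-week intervals, 63 × 0.05 = 3.2 per arm leave before the week-12 score. If it is all during treatment, the figure is 12 to 13 per arm. With 63 × 0.8 = about 50 per arm analysed, power at 1.1 is 0.785; with all 63 observed it is 0.870.

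**3. The two sections side by side, for someone who leaves before week 12.**

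| Section | Treatment of this participant |
|---|---|
| Datasets (FAS) | No postbaseline evaluation, so excluded |
| Withdrawal | Last result is final; analysed in the full dataset, so baseline is carried and the change is 0 |

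How far the two readings differ depends on assumed early loss, using the assumed changes of 6 and 4.9:

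- 5% lost early in both arms: 0.05 × (6 − 4.9) = 0.055 points.
- 5% lost early in the pill arm and none in control: 0.05 × 6 = 0.30 points, or 27% of 1.1.

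**4. LOCF after week 12.** Assumptions, none of them in the article: both arms truly change by 4.9; half of that is reached by week 12; recovery is linear from there to week 48; late loss is 25% in one arm and 15% in the other.

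Shift = (0.25 − 0.15) × 4.9 × (share of recovery still to come when the score is frozen)

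- All frozen at week 12: 0.10 × 4.9 × 0.5 = 0.245, or 22% of 1.1.
- Leavers spread evenly over last scores at weeks 12, 24 and 36: the shares still to come are 0.500, 0.333 and 0.167, mean 0.333. Then 0.10 × 4.9 × 0.333 = 0.163, or 15% of 1.1.

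The shift counts against the arm that loses more. Equal loss also costs something: with true changes of 6 and 4.9 and 20% of each arm frozen at half its recovery, the difference becomes 1.1 × (0.8 + 0.2 × 0.5) = 0.99 and power falls from 0.87 to 0.79.

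Steps 2 and 4 are alternatives. Each uses up the 20% dropout allowance, so they must not be added.

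**5. The opposite direction.** Suppose a share x of the pill arm alone is absent from the analysis and its change is g points worse than that of the rest. The spurious benefit is x × g: 0.05 points at x = 5%, g = 1; 0.20 at x = 10%, g = 2; 0.60 at x = 20%, g = 3. Both x and g are assumptions. Freezing works against the arm with more loss, while omitting poor responders works for it, so the article does not determine the net sign.

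**The case against.** A reader might infer that these rules act only in the pill arm and strip its non-compliers from the primary analysis. The article does not support that, for four reasons.

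- The FAS and LOCF rules are worded alike for both arms, and late ineligibility, prohibited medication and missed visits can occur in either. Only the exposure, compliance and stopping rules point to the pill. Even there, the compliance rule refers to prescribed medication, and controls are prescribed conventional drugs. That these rules fall mainly on the pill arm is a reasonable inference, not a stated fact.
- The elimination section names no analysis set. Its eligibility and deviation grounds largely overlap the per-protocol conditions, and the FAS definition contains none of them. It may be meant for the per-protocol set alone.
- Withdrawn participants are not simply discarded, since their efficacy data go into the full dataset.
- The first scheduled drug count is at week 12, when NIHSS is also taken. Someone found non-compliant at that visit already has a qualifying score.

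Two other readings also go too far. The article never claims an intention-to-treat analysis, so the fault is in the rules and not in a false label. Nor does it say that a participant who dies keeps the last NIHSS; it gives no specific rule for NIHSS after death.

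It can also be said that LOCF's limits are disclosed, that multiple imputation is promised, and that the analysis plan stays open until database lock. An early-termination assessment may exist in the full protocol. The article's own phase definition ends recovery at 6 months after onset, so freezing a score at week 24 or later may cost less than the linear assumption implies.

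These points limit the size and certainty of the bias. They leave standing the conditional FAS, the conflict over early leavers, the equating of stopping treatment with withdrawal, and the choice of LOCF as primary. The multiple imputation is described inside the FAS definition and, as written, does not bring back anyone outside it.

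**Conclusion.** The point holds in limited form. As written, the primary analysis is not of all participants as randomised, and the datasets, withdrawal and elimination sections cannot all be followed for someone who leaves before week 12.

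The size rests on assumptions the article neither gives nor excludes. LOCF alone shifts the difference by about 0.16 to 0.25 points, 15-22% of 1.1, given a 10-point imbalance in late loss and half of the recovery reached by week 12. The shift would be smaller if loss is balanced or recovery is nearly complete by week 12, and larger if the imbalance is greater. The net direction is unknown, so the article shows no bias in favour of the pill. The follow-up part is the more urgent, because recruitment began in April 2025 and uncollected scores cannot be replaced.

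**What to change.** 1. Define the primary set as all randomised participants, analysed by assigned arm.
2. Separate stopping treatment from stopping follow-up. Keep collecting NIHSS at the scheduled visits to week 48 from everyone who still consents, whatever their adherence. This concerns data collection only and leaves the rules for stopping treatment as they are.
3. State that the elimination and non-compliance criteria affect only the per-protocol set, and reconcile the elimination, withdrawal and datasets sections, in particular for people with no score after baseline.
4. Make a mixed model for repeated measures on weeks 12 to 48, or multiple imputation by arm with baseline NIHSS, the primary handling of missing scores. Keep LOCF as a sensitivity analysis. The chosen method must cover participants with no postbaseline score.
5. Prespecify how deaths enter the NIHSS analysis. Assigning the worst score is one option but a debatable one, since extreme values would weigh heavily on a mean with an assumed SD of 2.

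The cost is a protocol amendment, wording in the analysis plan before it is finalised, and some effort to follow participants who have stopped treatment. The visits are already scheduled. Off-treatment scores may dilute the estimate slightly.
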